#### Secondary Outcome Measures

1. Total, MCS, and 8 individual dimensions and subscales of the SF-36™ (version 4.0) for confirmation and clarification of the primary outcome results.

2. ODI (cross-cultural adaption of the ODI version 2.1 for use with German-speaking patients)[24]: this is one of the condition-specific questionnaires recommended for use with back pain patients. The ODI is a standardized, patient-completed questionnaire which gives a subjective percentage score of level of function (disability) in activities of daily living for those rehabilitating from low back pain. The questionnaire examines perceived level of disability in 10 everyday activities of daily living.

3. COMI questionnaire (version 2008): a patient-oriented, short, multidimensional outcome instrument validated for patients with spinal disorders.

4. X-rays will be taken after 6 weeks, 6, 12, 24, and 36 months. Further assessments will be performed annually. These are common intervals after surgical implant procedures not requiring extraneous radiation. At the point in time where adjacent instability is identified radiographically, we will reevaluate and compare the clinical outcome. Criteria for radiologic ASD as well as adjacent instability are listed in the appendix (definition of radiologic instability and Weiner's classification). Pre- and postoperative x-rays must be compared to assess the Weiner's classification score. X-rays will be evaluated by experienced radiologists.

5. Clinical ASD will be assessed (see appendix for the definition).

6. Work-related function/disability at the time of surgery and after surgery, plus the duration until return to work. At each visit, patients will be interviewed about their level of work-related function/disability as well as the time point when/if they return to employment.

7. Inpatient mortality and mortality at 6 months.

8. Surgery-related data (blood loss, length of incision, duration of surgery) are taken from the surgical report.

9. Intraoperative and postoperative complication rates (e.g. implant failure)

10. Adverse events (AE) and serious adverse events (SAE) will be documented and monitored throughout the study.

### Sample size

Our target recruitment is 30 patients. We assume a loss of follow-up of 10%, so that 27 patients should be available for the final analysis. The normalized form of the SF-36™ PCS (mean 50, standard deviation 10) is assumed. With this number of patients, using a two-sided t-test, a normalized PCS score difference of 11.2 or more could be detected with a power of 80% and alpha = 0.05.

### Randomization

The randomization of patients into intervention and control groups will be performed using blocks of randomly variable length in order to maintain balance while preventing predictability of allocation. Randomization is stratified by surgeon. A container with the sequentially numbered, sealed envelopes is stored in a locked cupboard, which only the investigator(s) can open. The random allocation sequence and the sealed envelopes will be generated by the Institute of Medical Statistics, Informatics, and Epidemiology of the university conducting the trial. Enrollment and randomization will be executed by the investigator.

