### Data analysis

The PCS and MCS sub-scores and the ODI score are measured repeatedly; thus, areas under the curve (AUC) will be computed. AUCs will be compared between treatment groups using a two-sample t-test.

Time until ASD or adjacent segment instability will be analyzed using the life-table method and compared between treatment groups using the log-rank test.

The primary analysis set is defined according to the intention-to-treat principle, including all randomized patients and interpolating missing longitudinal data. Robustness of results will be investigated by additional analyses based on the per-protocol set. Interim analyses are not foreseen.

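### Randomisation is stratified by surgeon but the planned t-test and log-rank test omit surgeon; if surgeons differ in outcome, the t-test is conservative and gives up some precision

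*Protocol article*

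**What the plan says.** The Randomization section of the protocol article describes "blocks of randomly variable length in order to maintain balance while preventing predictability of allocation", and then states: "Randomization is stratified by surgeon".

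The Data analysis section turns the repeated PCS, MCS and ODI scores into areas under the curve and says: "AUCs will be compared between treatment groups using a two-sample t-test". Time to adjacent segment disease or instability is to be "compared between treatment groups using the log-rank test". Neither sentence mentions surgeon, and no surgeon term appears elsewhere in the article.

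The Sample size section rests on the same unadjusted test: "using a two-sided t-test, a normalized PCS score difference of 11.2 or more could be detected with a power of 80% and alpha = 0.05". Its inputs are "Our target recruitment is 30 patients", "We assume a loss of follow-up of 10%, so that 27 patients should be available for the final analysis" and "The normalized form of the SF-36™ PCS (mean 50, standard deviation 10) is assumed".

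The article does not give the number of surgeons, the block sizes or any expected variation between surgeons.

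**The concern.** Blocking within surgeon keeps the two arms close to balanced for each surgeon, so differences between surgeons largely cancel out of the treatment comparison. An ordinary two-sample t-test does not know this. It counts the between-surgeon spread as patient-level error, so its standard error is larger than the real sampling variation of the treatment difference. The p-value is then too large and the confidence interval too wide.

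With about 27 patients analysed and a detectable difference of more than one standard deviation, an interval wider than necessary is unwelcome. It also bears on the Objective section's question of whether topping off is better than, or at least equivalent to, fusion. The same reasoning applies in principle to the log-rank test.

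**Working it through.** **1. The plan's own figure.** Inputs from the Sample size section: 27 patients (taken as 13 and 14), SD 10, two-sided alpha 0.05.

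- Standard error: 10 × √(1/13 + 1/14) = 3.85.
- Noncentrality at 11.2 points: 11.2 / 3.85 = 2.91, with 25 degrees of freedom.
- Power from the noncentral t distribution: 79.8%. The difference detectable with 80% power is 11.23.

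The stated 11.2 reproduces. A normal approximation would give 10.8, so the plan used the t distribution.

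**2. The mechanism.** Let ρ be the share of the total variance that lies between surgeons. With perfect balance within surgeon, the true standard deviation of the treatment difference is about 3.85 × √(1 − ρ). For ρ = 0.2 that is 3.85 × 0.894 = 3.45. The pooled t-test does not apply this reduction.

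**3. Simulation.** From the article: 27 patients, SD 10, difference 11.2, alpha 0.05. Assumed: 2, 3 or 5 surgeons, each patient equally likely to be under any of them; permuted blocks of 2, 4 or 6 within surgeon; ρ from 0 to 0.4 with total SD held at 10. The comparison is the unadjusted t-test against a linear model with treatment and surgeon as a factor. There were 20,000 trials per setting for alpha (Monte Carlo standard error √(0.05 × 0.95 / 20,000) = 0.0015) and 10,000 for power (about 0.004). Ranges are over the number of surgeons.

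| ρ | Alpha, t-test | Alpha, with surgeon | Mean t-test SE | True SD of difference | Power at 11.2, t-test | Power at 11.2, with surgeon |
|---|---|---|---|---|---|---|
| 0 | 0.050–0.052 | 0.050–0.051 | 3.81–3.83 | 3.85–3.87 | 79–80% | 78–80% |
| 0.05 | 0.047–0.049 | 0.049–0.052 | 3.77–3.81 | 3.75–3.79 | 80–81% | 79–81% |
| 0.1 | 0.042–0.046 | 0.049–0.052 | 3.72–3.79 | 3.66–3.71 | 81–82% | 82–83% |
| 0.2 | 0.035–0.041 | 0.048–0.051 | 3.61–3.75 | 3.46–3.52 | 82–85% | 85–87% |
| 0.4 | 0.025–0.032 | 0.048–0.051 | 3.39–3.67 | 3.02–3.15 | 86–89% | 94–95% |

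At ρ = 0.2 the t-test's standard error is about 4% to 7% too large (3.61/3.46 = 1.04 with two surgeons, 3.75/3.52 = 1.07 with five). Adjusting raises power by 2.8 points with two surgeons (84.6% to 87.4%), 4.0 with three (82.9% to 86.9%) and 3.2 with five (82.2% to 85.4%). With five surgeons and ρ = 0, adjusting lowers power from 79.6% to 77.7%.

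**4. Log-rank test.** For illustration: 30 patients, 36 months of follow-up, and the 24% rate at an average of 39 months cited in the Background. Expected events without a surgeon effect are 30 × (1 − 0.76^(36/39)) = 6.7. The spread of the log hazard between surgeons is assumed; 10,000 trials per setting.

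| SD of surgeon log hazard | Alpha, unstratified | Alpha, stratified |
|---|---|---|
| 0 | 0.047–0.051 | 0.045–0.049 |
| 0.5 | 0.042–0.048 | 0.044–0.049 |
| 1.0 | 0.032–0.036 | 0.043–0.056 |

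The two tests separate only when surgeons differ very strongly.

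**The case against.** **The effect is conditional.** With no surgeon effect the t-test is correctly calibrated, and at a 5% share the loss is negligible. The Intervention group section sets a minimum of 30 fusions per surgeon and adds intraoperative photographs and a teaching film, all of which may keep surgeons alike. The trial is also at a single hospital and its outcome is patient-reported. This stands, and it limits the size of the point.

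**The plan does not say that surgeons differ.** A reader might infer that stratifying by surgeon amounts to assuming a surgeon effect. The article gives balance and unpredictability as reasons for blocking, and no reason for choosing surgeon. The inference is not supported.

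**No stated figure fails.** A reader might infer that the trial falls short of its promised power. In the settings examined, unadjusted power stays at about 80% or rises above it. What is given up is a possible gain.

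**The power figures are not for the AUC.** SD 10 is the value for a single PCS measurement. The AUC's standard deviation and surgeon share are not given. Type I error does not depend on the scale, but the power figures do.

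**The full protocol or SAP may add surgeon.** It may, and a pooling rule is normally a matter for the SAP. But the article names the two-sample t-test outright for the AUC comparison and sizes the trial on a t-test, so a surgeon term would depart from what it states.

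**Conclusion.** The mismatch between randomisation and analysis is certain from the text; its consequence is conditional and modest. If surgeons differ in outcome, the planned t-test is conservative: at a 20% share, true alpha is roughly 0.035–0.041 in place of 0.05, and about 3 to 4 points of power at 11.2 are left unused. At a 10% share the unused power is about 1 to 1.5 points, and at 5% or below the effect can be ignored. For the log-rank test little changes unless surgeon effects are very large.

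A reader might infer that the test is invalid, or that false positives are inflated. Neither follows: no setting with a surgeon effect gave a type I error above 0.05 for the unadjusted t-test.

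The sizes rest on assumed numbers of surgeons, block lengths and variance shares, and the power figures also on SD 10. This is a cheap improvement: severity minor, confidence moderate.

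**What to change.** In the Data analysis section, replace the two-sample t-test on the PCS, MCS and ODI AUCs with a linear model containing treatment and surgeon (the randomisation stratum), and report the adjusted difference with its confidence interval. State that surgeons with very few patients will be pooled by a rule fixed before data release. For consistency, stratify the log-rank test by the same surgeon groups.

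The change is to wording only and needs no extra patients or data. The price is one degree of freedom per additional surgeon, so with 27 patients the residual degrees of freedom fall from 25 to between 24 (two surgeons) and 21 (five). The worst case examined, five surgeons and no surgeon effect, costs about 2 points of power; pooling sparse surgeons would reduce the degrees of freedom spent.

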### Data analysis

The PCS and MCS sub-scores and the ODI score are measured repeatedly; thus, areas under the curve (AUC) will be computed. AUCs will be compared between treatment groups using a two-sample t-test.

Time until ASD or adjacent segment instability will be analyzed using the life-table method and compared between treatment groups using the log-rank test.

The primary analysis set is defined according to the intention-to-treat principle, including all randomized patients and interpolating missing longitudinal data. Robustness of results will be investigated by additional analyses based on the per-protocol set. Interim analyses are not foreseen.

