### Outcome measures and assessments

#### Primary Outcome Measures

The focus of this investigation is on subjective and objective clinical benefits for the patient. Functional outcomes will be evaluated using the SF-36™ score after 6 weeks as well as 6, 12, 24, and 36 months after surgery. The SF-36™ is the most frequently used generic health status measure worldwide. In the past, spine surgery investigations have focused on technical outcomes; however, more recently they have turned to clinical results [20,21]. It is unclear whether radiologic parameters correlate with clinical success; thus, they are poor measures of primary outcome. Recent, important randomly controlled trials (RCTs) in spine surgery have used the SF-36™ and ODI tools to assess clinical outcomes [22,23]. Parameters like pain and walking distance are represented in the SF-36. The development of physical (PCS) and mental health (MCS) component scores has eased interpretation and cross-cultural comparison of the SF-36™. The SF-36™ is a standardized questionnaire to detect patient quality of life corresponding to conditions of health. It yields an 8-scale profile of functional health and well-being scores, as well as psychometrically-based physical and mental health summary measures, and a preference-based health utility index. Thus, the SF-36™ and the patient responses contained within are a good measure of primary endpoint. Points are awarded for individual answers by each patient and added to yield a sum total. The SF-36™ PCS scores of the experimental and control groups will be compared to further quantify patient outcome. Subsequent follow-up will repeat the SF-36™ to ensure assessment for clinical impairment and/or the manifestation of a clinical or radiologic instability. This follow-up will continue for up to 3 years and further after treatment. In cases of impairment, x-ray is medically indicated at any point of time.

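### The AUC t-test makes no use of the preoperative score; with about 13 v 14 patients, a baseline-adjusted model would be a cheap gain in precision of uncertain size

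*Protocol article*

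**What the plan says.** Under Primary Outcome Measures the article gives the assessment times: "Functional outcomes will be evaluated using the SF-36™ score after 6 weeks as well as 6, 12, 24, and 36 months after surgery". All of these fall after surgery. The group comparison is of the physical component score: "The SF-36™ PCS scores of the experimental and control groups will be compared to further quantify patient outcome".

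Under Data analysis: "The PCS and MCS sub-scores and the ODI score are measured repeatedly; thus, areas under the curve (AUC) will be computed". The next sentence fixes the test: "AUCs will be compared between treatment groups using a two-sample t-test". No covariate, change score or baseline-corrected AUC is named.

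Under Randomization, surgeon is the only stratification factor.

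The Sample size section rests on an unadjusted test too. The target is 30 patients, and "We assume a loss of follow-up of 10%, so that 27 patients should be available for the final analysis". It continues: "The normalized form of the SF-36™ PCS (mean 50, standard deviation 10) is assumed"; "using a two-sided t-test, a normalized PCS score difference of 11.2 or more could be detected with a power of 80% and alpha = 0.05".

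**The concern.** Two patients with very different preoperative PCS are treated alike by this comparison. Stratifying by surgeon does not balance the preoperative score, and the t-test does not account for it afterwards. In a large trial this would matter little. With 13 and 14 patients, the arms can easily differ by several points before surgery, and part of that difference carries over into the postoperative AUC.

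Two things are at stake. One is precision: variation between patients that the preoperative score could explain stays in the error term. The other is how the single realised result reads: if the arms happen to differ at baseline, the unadjusted difference is shifted in a known direction and the planned analysis does not correct it.

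**Working it through.** **Inputs from the article.** 27 evaluable patients, taken as 13 v 14 (the allocation ratio is not stated; 1:1 is assumed); PCS SD 10; two-sided alpha 0.05; power 80%; visits at 6 weeks and 6, 12, 24 and 36 months.

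**Assumptions not in the article.** Baseline SD 10; a common visit-to-visit correlation r among postoperative visits; a common pre/post correlation p between the preoperative score and each postoperative visit. Both the 36-month and the 6-month windows are shown, because the Data analysis section does not name the AUC window.

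**1. The plan's own figure.** Noncentral t, SD 10, 25 df: the detectable difference is 1.123 × 10 = 11.23, and power at 11.2 is 79.8%. The stated 11.2 reproduces, and it rests on an unadjusted test.

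**2. Chance imbalance.** SE of the baseline difference = 10 × √(1/13 + 1/14) = 3.85 points. The 95% range is ±1.96 × 3.85 = ±7.5 points, and a difference above 5 points occurs in about 19% of such trials. With equal SDs, the regression slope of the time-averaged AUC on baseline is p, so the part that reaches the estimate has a 95% range of p × 7.55:

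- p = 0.2: ±1.5 points
- p = 0.3: ±2.3 points
- p = 0.5: ±3.8 points

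**3. Variance of the AUC divided by window length.** With trapezoid weights w, V = Σw²(1 − r) + r in units of SD².

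- 6 weeks (1.38 months) to 36 months: w = 0.067, 0.153, 0.260, 0.347, 0.173; Σw² = 0.246. At r = 0.5, V = 0.623, SD = 7.89, detectable difference 1.123 × 7.89 = 8.86.
- 6 weeks to 6 months: w = 0.5, 0.5; Σw² = 0.5. At r = 0.5, V = 0.75, SD = 8.66, detectable difference 1.123 × 8.66 = 9.72.

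**4. After adjustment.** Effective SD = 10 × √[(V − p²)(1 + 1/23)], with 24 df. The factor 1 + 1/23 is the cost of estimating the slope, and the multiplier becomes 1.125. With r = 0.5:

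| Window | p | Effective SD | Detectable difference | Power at 8 points |
|---|---|---|---|---|
| 36 months | unadjusted | 7.89 | 8.86 | 71.6% |
| 36 months | 0.2 | 7.80 | 8.77 | 72.4% |
| 36 months | 0.3 | 7.46 | 8.39 | 76.2% |
| 36 months | 0.5 | 6.24 | 7.02 | 89.1% |
| 6 months | unadjusted | 8.66 | 9.72 | 63.5% |
| 6 months | 0.2 | 8.61 | 9.68 | 63.9% |
| 6 months | 0.3 | 8.30 | 9.33 | 67.1% |
| 6 months | 0.5 | 7.22 | 8.12 | 78.8% |

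The 8-point difference is illustrative and does not come from the article.

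**5. Sensitivity to r.** For the 36-month window with p held at 0.3, the detectable difference falls from 7.71 to 7.10 at r = 0.3, from 8.86 to 8.39 at r = 0.5, and from 9.88 to 9.50 at r = 0.7.

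**The case against.** The strongest reply is that nothing here is an error. A t-test between randomized arms is unbiased over repeated randomizations, keeps its 5% type I error, and already carries chance imbalance in its standard error. A reader might infer that the planned test is invalid or biased; the documents do not support that. The same holds for the idea that baseline imbalance passes in full into the result: it enters only in proportion to the pre/post correlation.

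Second, the gain depends on correlations that the article does not give. A large gain appears only if the preoperative score correlates well with scores up to 36 months later, with surgery in between. If one value of 0.5 is used for both correlations, power at 8 points rises to 89%, and a reader might take that as the expected benefit. With pre/post 0.3 it is 76%, and with 0.2 there is practically no gain. This stands, and the size can be stated only as a range.

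Third, at the article's own 11.2 points the unadjusted AUC test already has about 94% power (36 months) or 90% (6 months) under the model above with r = 0.5. This also stands: the planned target does not depend on adjustment.

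Fourth, a reader might infer that no preoperative questionnaire is taken, or that the QALY calculation lacks a starting value. A condensed article may simply leave a baseline visit to the full protocol, so neither can be claimed.

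The choice of test survives all four replies. It is stated in the article, not left open, and it makes no use of the preoperative score.

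**Conclusion.** The point holds as a recommended improvement in efficiency, not as a fault in validity. The article fixes an unadjusted comparison in a trial small enough for preoperative imbalance to matter, and neither the stratification nor the test deals with it. What is lost is precision, together with a shift in the realised estimate that depends on the imbalance.

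The size runs from negligible at a pre/post correlation of about 0.2 or less, through about half a point of detectable difference at 0.3, to nearly two points at 0.5 (36-month AUC, visit-to-visit correlation 0.5). This rests on a baseline SD of 10, equal SDs at all visits, constant correlations and a 13 v 14 split. Only the SD of 10 for PCS and the total of 27 come from the article. The calculation was made for PCS; for MCS and ODI the reasoning carries over but the figures do not.

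**What to change.** Replace the two-sample t-test with a linear model of the postoperative AUC, divided by window length, on arm and the preoperative value of the same score. Report the adjusted difference with its 95% confidence interval. Do the same for MCS and ODI.

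If the full protocol already collects SF-36 and ODI before surgery, only the wording of the analysis changes. If it does not, add both before randomization; a preoperative score cannot be obtained later.

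Two apparent substitutes do not do the same job. Starting the AUC at the preoperative value gives that value a weight of about 2% (36 months) or 12% (6 months) and adds the imbalance to the outcome. Subtracting the preoperative score changes the variance from V to V + 1 − 2p, which is a gain only when p exceeds 0.5.

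The cost is one degree of freedom, possibly one extra set of questionnaires, and a revised sentence. If the pre/post correlation proves to be about 0.2 or less, the gain is negligible; with no correlation at all, precision is slightly worse than with the t-test.

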### Participants and recruitment

Patients over 30 years of age presenting to our outpatient clinic with degenerative disc disease or spondylolisthesis and indications for monosegmental lumbar spine fusion are eligible for trial inclusion. Surgery will not be considered until at least 6 months of conservative treatment have been concluded. Patients with spondylolisthesis must respond positively to facet joint injection. Radiologic inclusion criteria are summarized in the appendix.

Prerequisite to inclusion is the presence of radiologic degeneration of the adjacent segment (Pfirrmann grades II-IV in MRI findings [18]) without signs of instability. Definition of radiologic and clinical instability as well as further inclusion criteria are summarized in the appendix.

Study subjects will be approached and recruited by experienced spine surgeons. For the screening procedure, an estimated 150 patients per year will undergo primary monosegmental fusion within the department. Recruitment of approximately 30 patients per year is anticipated.

Patients participating in parallel interventional studies as well as patients with lumbar scoliosis (> 25° cobb angle), spondylolisthesis Meyerding IV, and/or radiologic ASD worse than Fujiwara grade II or Pfirrmann grade IV [18,19] are excluded from this study. Further exclusion criteria are summarized in the appendix.

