## Discussion

New hybrid systems might improve the outcome of lumbar spine fusion. To date, however there is no convincing published data regarding these topping off systems. High quality data is required to provide a preliminary impression of the advantages and disadvantages of such devices. If only because topping off devices are quite expensive compared to conventional implants, nonessential use should be avoided. In fact, these high costs necessitate efforts by health care providers to examine the effects of these implants. Randomized clinical trials are highly recommended to evaluate the benefits or harm to patients.

In the intervention group, the approach to the spine will be enlarged compared to that of the monosegmental fusion group. The longer approach itself could bring about a negative outcome compared to that of regular fusion (e.g., due to muscle damage, blood loss, higher risk of infection). As well, implant failure rates can be compared between the groups. The crucial question, however, is the ability to prevent ASD.

Placebo is not an acceptable option for the control group for fundamentally ethical reasons. Not only would such an option deprive the patient of adequate treatment, but also to have a realistic placebo would require an invasive procedure without the implantation of a medical device, thus exposing him/her to significant risks without providing benefit. Furthermore, a "placebo device" as replacement for the respective topping-off system does not exist.

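### The log-rank comparison of time to ASD is valid but ignores the baseline Pfirrmann grade of the adjacent segment, which is known for every patient and not balanced by randomization

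*Protocol article*

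**What the plan says.** The Data analysis section of the protocol article fixes the method for ASD: "Time until ASD or adjacent segment instability will be analyzed using the life-table method and compared between treatment groups using the log-rank test". It names no stratification factor and no covariate.

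Participants and recruitment makes entry depend on the "presence of radiologic degeneration of the adjacent segment (Pfirrmann grades II-IV in MRI findings [18]) without signs of instability", and the inclusion criteria in the Appendix repeat the grade range. The grade is therefore read before randomization in every patient, and three grades are admitted.

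Under Randomization the only factor is surgeon: "Randomization is stratified by surgeon". The sample size section gives the scale: "Our target recruitment is 30 patients".

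ASD is listed among the secondary outcomes, yet the Discussion says of it: "The crucial question, however, is the ability to prevent ASD".

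**The concern.** The events are changes in, or symptoms from, the segment that was graded at entry. If starting grade affects the chance of an event, and the arms differ in grade by chance, the two curves will differ without any device effect, or a real effect will be masked. In a trial of 30 such a difference is not rare, and neither the allocation nor the described test accounts for it.

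What is at stake is how far the realised ASD result can be believed. Few events are expected. If the baseline table shows a clear grade imbalance and no adjustment was prespecified, any later adjustment is post hoc and open to challenge, whichever way it moves the result.

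**Working it through.** **The plan's own figures.** 30 × 0.9 = 27 analysable patients. A two-sample t-test with 13 v 14 patients, SD 10, two-sided alpha 0.05 and 80% power detects 11.23 points, against the stated 11.2. That figure reproduces, but it concerns the SF-36 physical component score. The article gives no event count, hazard ratio or power for the log-rank test, so there is nothing to reproduce there.

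**Inputs from the article.** N = 30 (Sample size). Grades II-IV (Participants and recruitment, Appendix). X-rays at 6 weeks and 6, 12, 24 and 36 months (Secondary Outcome Measures). ASD rates of 16.5%, 24% and 42.6% (Background).

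**Assumptions.** 15 patients per arm, inferred from balanced blocks because no ratio is stated. The share of each grade. The strength of grade as a predictor. The three ASD rates are used as 36-month risks to span a range, although they were reported at 5 years, 39 months and 7.8 years.

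**How likely is an imbalance?** With 15 grade IV patients among 30 and 15 per arm, P(k in control) = C(15,k)² / C(30,15), and C(30,15) = 155,117,520.
- Ten or more in control: (9,018,009 + 1,863,225 + 207,025 + 11,025 + 225 + 1) / 155,117,520 = 0.072.
- Either direction: 2 × 0.072 = 0.143.
- If only 10 of 30 are grade IV, a split of 7:3 or worse in either direction has probability 0.245.

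**How many events?** 30 × 0.165 = 5.0; 30 × 0.24 = 7.2; 30 × 0.426 = 12.8.

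**What does an imbalance do to the test?** Each setting used 20,000 simulated trials, 15 v 15, one third of patients per grade, events found at the visits above and no dropout. The hazard ratio (HR) per grade step was 1, 2 or 3. In each cell the unstratified test comes first, then the test stratified by the three grades. The middle column is the one-sided false-benefit rate in trials where control had at least 4 more grade IV patients (about 8-9% of trials).

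| ASD risk | HR per grade | False benefit, imbalanced trials, no device effect | Two-sided size, all trials | Power, device HR 0.33 |
|---|---|---|---|---|
| 16.5% | 1 | 2.5 / 2.7% | 4.4 / 4.5% | 10.3 / 10.3% |
| 16.5% | 2 | 5.1 / 2.3% | 4.2 / 4.5% | 10.9 / 10.9% |
| 16.5% | 3 | 6.5 / 1.8% | 4.2 / 4.7% | 9.9 / 10.8% |
| 24% | 1 | 2.4 / 1.9% | 4.6 / 4.6% | 18.3 / 16.9% |
| 24% | 2 | 5.6 / 2.5% | 5.0 / 5.2% | 17.6 / 17.3% |
| 24% | 3 | 8.5 / 2.5% | 4.9 / 5.2% | 17.2 / 17.9% |
| 42.6% | 1 | 2.2 / 2.3% | 5.2 / 5.2% | 34.2 / 31.6% |
| 42.6% | 2 | 7.2 / 2.5% | 5.0 / 5.1% | 32.8 / 32.7% |
| 42.6% | 3 | 10.5 / 1.6% | 5.0 / 5.3% | 29.4 / 33.3% |

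With two strata (II-III v IV) and a grade IV hazard ratio of 4 to 8, false benefit in the imbalanced trials is roughly 7-15% unstratified and 1-5% stratified. Power changes by about −2 points if grade is not prognostic and by up to about +9 if it is strongly so.

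**The case against.** **The test is valid and the article is condensed.** An unstratified log-rank test is a standard choice for a secondary outcome, and chance imbalance is already inside its 5% error. The table bears this out: overall size is 4.2-5.2% for the planned test. A reader might infer that the test is biased or its error rate inflated; the calculations do not support that. The analysis plan may also already adjust for grade. This stands, and it limits the point to an improvement.

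**The gradient is not documented.** Nothing in the article says how strongly Pfirrmann grade predicts ASD. It is tempting to illustrate with 36-month risks of 5% v 35%, where a 10:5 split gives 10 × 0.35 + 5 × 0.05 = 3.75 events against 5 × 0.35 + 10 × 0.05 = 2.25, an apparent 40% reduction. But those risks imply a hazard ratio of ln(0.65)/ln(0.95) = 8.4, which is a strong assumption. With no gradient the excess disappears.

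**Higher grade need not mean nearer to every event.** A reader might infer that a grade IV disc is closer to all of them. The Appendix does not support this: Weiner's scale runs from 0 to 3, so a segment starting at 2 or 3 cannot worsen by two grades. Complete collapse points the other way, and most other instability criteria concern displacement, angulation or rotation. Direction may differ by component. Stratifying does not require knowing it.

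**The overall effect is small.** Frequency times excess gives 0.091 × (5.6 − 2.5) = 0.28 percentage points (24% risk, HR 2 per grade) and 0.083 × (10.5 − 2.5) = 0.66 points (42.6%, HR 3). That is correct as an average over randomizations. It does not help the sponsor whose one trial turns out imbalanced.

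**Conclusion.** The point holds as a cheap improvement to a secondary analysis, not as an error in the planned test. The described comparison leaves unused a baseline value that every patient has, that belongs to the segment under study and that randomization does not balance.

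Its size is conditional. If half the patients are grade IV, a 10:5 split or worse occurs in about 14% of trials, half of these against control. In trials with a clear excess of grade IV in control, one-sided false benefit is roughly 4-7% for a moderate gradient and up to about 10-15% for a strong one, against 2.5%. By symmetry the opposite imbalance can hide a benefit.

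This rests on 15 per arm, on the assumed grade mix and on grade being prognostic. None of the three is stated in the article, and without the last there is no excess. The case is about credibility of the realised result; neither overall type I error nor power is a strong argument.

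**What to change.** In Data analysis, prespecify for time to ASD or adjacent instability a log-rank test stratified by baseline Pfirrmann grade of the adjacent segment (II-III v IV), or a Cox model with grade as the single covariate. Say whether it is the main or a supportive ASD analysis. Report the grade distribution by arm and ASD events by arm within grade. If the analysis plan already does this, a sentence saying so is enough.

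The cost is one or two sentences; the grade is already collected for eligibility. With about 5 to 13 events expected, a stratum with few events adds little, which is why two strata are preferable to three: three strata lost up to 34.2 − 31.6 = 2.6 points of power when grade was not prognostic. With two strata the change is about −2 to +9 points, and overall type I error stays near 5%.
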